#### Qualitative Research

Participants assigned to the intervention group will be invited to take part in in-depth interviews both before and after the HIIT intervention. Trained interviewers will administer these interviews either in person during scheduled study visits or via Zoom within 1 week of the visits if participants are unable to attend in person. The interviews will be guided by interview guides specifically developed for the study and piloted with members of the study team. Preintervention interviews will delve into participants’ prediabetes history, physical activity and dietary habits, perceptions of body size and image, as well as their comfort levels, perceived difficulty, confidence, and expectations regarding the HIIT intervention. Post-intervention interviews will focus on participants' experiences with the intervention. Every effort will be made to interview both dropouts and active participants to ensure a comprehensive understanding of program acceptability and to identify barriers and facilitators to adherence. All interviews will be audio recorded, transcribed verbatim, and deidentified for analysis.

### Outcomes

#### Primary Outcomes

Quantitative measures: (1) feasibility metrics and (2) mean FIM, TFA, and IAM scores.

Qualitative measures: participants’ experiences, perceptions, and satisfaction with the HIIT intervention, and facilitators and barriers to participation.

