### Intervention

Following the recommendation of the American College of Sports Medicine [38], participants in the intervention group will be required to obtain medical clearance from their general practitioner before starting the HIIT sessions. These sessions, led by a qualified exercise physiologist (the instructor) and adhering to standard protocols [39,40], will take place in the Aerobic Exercise Laboratory at Emory University's Rehabilitation Hospital. Using “spin cycle ergometers” (Schwinn), sessions will be conducted in small groups of 5 or fewer participants at specified times on Mondays, Wednesdays, and Fridays, spanning 8 weeks. Each participant will undergo a maximum of 24 HIIT sessions. Each session will consist of a 5-minute warm-up, followed by an interval-based workout phase with steady up-tempo cadences, sprints, climbs, and interspersed recovery periods. A 5-minute cooldown will conclude each session. The workout sessions will initially last 20 minutes and will progressively increase in time based on participants’ tolerance and instructor recommendations. Each session will include “active rest” periods where resistance is reduced to lower HR, alternating with high-intensity intervals featuring sprints or climbs to elevate HR. The duration of active rest versus high-intensity intervals will be adjusted according to individual responses and target HR. To monitor and maintain intensity within the target HR range, participants will wear Polar H10 chest strap HR sensors [41]. The target HR will be calculated using the Karvonen method [42]. Exercise intensity will begin at 75% of the estimated maximum HR reserve (HRR) and will increase by 5% every week, as tolerated or deemed necessary by the instructor, over the 8-week intervention period. During the workout phase, the target HRR reserve will be maintained by averaging increases and decreases in intensity or HR with a target to maintain within a 10% offset from the HRR goal [39,40]. Participants will need to adhere to within-session HR targets at an 80% rate (or greater) for a session to be counted as attended and participants will need to attend 19 out of 24 sessions to be included as a “completer” in the final data analysis. To date, our interventions have yielded a within-session adherence rate to the prescribed intervention of 91% (as measured by HR) and a retention rate of 85% [40,43-45]. Participants’ weight and body composition will be measured weekly.

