### Procedures

The details about the measurements, study tools, and timelines are outlined in Table 1.

**Table 1 table1:** Measurements, study tools, and study timeline.

Variables	Components	Study tools	Baseline		8 weeks
Study feasibility	Response rate, screening yield, enrollment rate, time to enrollment, intervention compliance, resource use, and retention rate	REDCap^a^ database	✓		✓
Intervention feasibility	Qualitative and quantitative research	Feasibility of Intervention Measure [46]	✓		✓
Intervention feasibility	Qualitative and quantitative research	In-depth interviews	✓		✓
Intervention acceptability	Qualitative and quantitative research	Theoretical Framework of Acceptability questionnaire [47]	✓		✓
Intervention acceptability	Qualitative and quantitative research	In-depth interviews	✓		✓
Intervention appropriateness	Qualitative and quantitative research	Intervention Appropriate Measure [46]	✓		✓
Intervention appropriateness	Qualitative and quantitative research	In-depth interviews	✓		✓
Participants’ expectations of and experiences with the intervention	Qualitative research	In-depth interviews	✓		✓
Sociodemographics	Age, sex, marital status, education, and occupation	WHO STEPS^b^ [34] and NHANES^c^ questionnaires [35]	✓		x^c^
Eligibility criteria	Inclusion and exclusion criteria^e^	Short-form IPAQ^f^ [32]	✓		x
Behavioral measures	Dietary habits	ASA24^g^ dietary assessment tool [36]	✓^h^	✓^h^	
Behavioral measures	Physical activity	Short-form IPAQ [32]	✓^i^	✓^i^	
Behavioral measures	Smoking	WHO STEPS [34] and NHANES questionnaires [35]	✓		✓
Behavioral measures	Alcohol consumption	WHO STEPS [34] and NHANES questionnaires [35]	✓		✓
Physical measures	Height	Stadiometer	✓		x
Physical measures	Weight	Digital weighing scale	✓		✓
Physical measures	Waist circumference	Inelastic measuring tape	✓		✓
Physical measures	Hip circumference	Inelastic measuring tape	✓		✓
Physical measures	BP^j^	DINAMAP BP apparatus	✓		✓
Physical measures	Body composition	Bioimpedance analysis	✓		✓
Biochemical measures	OGTT^k^ (0, 30, and 120 minutes)	Enzymatic assays	✓		✓
Biochemical measures	Insulin levels at 0 and 30 minutes	Immunoassays	✓		✓
CGM^k^	Proportion of time and mean time spent in nocturnal (00:00-06:00) normoglycemia (60 to <100 mg/dl) [48]	Dexcom G6 Pro (DexCom, Inc)	✓^l^	✓^l^	

^a^REDCap: Research Electronic Data Capture.

^b^WHO STEPS: World Health Organization STEPwise approach to noncommunicable disease risk factor surveillance.

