### Intervention, Feasibility, Acceptability, and Appropriateness

The Feasibility of Intervention Measure (FIM) will evaluate the feasibility of the intervention, encompassing questions regarding its implementability, possibility, doability, and ease of use [46]. The acceptability of the intervention will be assessed through the Theoretical Framework of Acceptability (TFA) questionnaire, which explores affective attitude, burden, ethicality, perceived effectiveness, intervention coherence, self-efficacy, opportunity costs, and general acceptability [47]. The Intervention Appropriate Measure (IAM) will evaluate the appropriateness of the intervention, including questions about its fittingness, suitability, applicability, and alignment with participants’ needs [46]. Responses to the questions in all 3 questionnaires will be recorded on a Likert scale of 1 to 5. The mean total score for each of these scales will be calculated by combining the individual Likert points of each scale. Higher scores on the FIM, TFA, and IAM scales indicate greater feasibility, acceptability, and appropriateness, respectively, among participants.

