### Sample Size Calculation

Assuming a Cohen *d* of 0.3 to <0.7 (medium standardized effect size) [25,59] for FPG in the planned main trial, with an alpha of 5% and a power of 90%, a sample size of 15 participants per treatment group is deemed necessary for this pilot study. Factoring in a 10% loss to follow-up in each group, the total sample size was estimated to be 34 participants (17 per group).

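### HIIT participants who leave and miss the 8-week visit give no post-exposure FIM, TFA or IAM score, so these primary-outcome means risk upward bias

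*Protocol article*

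**What the plan says.** The Primary Outcomes section of the protocol article names as quantitative measures "1) feasibility metrics and (2) mean FIM, TFA, and IAM scores". The section on intervention feasibility, acceptability and appropriateness adds that "Responses to the questions in all 3 questionnaires will be recorded on a Likert scale of 1 to 5", with higher scores being more favourable.

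Table 1 (Procedures) ticks all three instruments at baseline and at 8 weeks. Other rows carry footnotes where the schedule or the arm differs (diet, physical activity, CGM). These three rows carry none. Under Randomization and Blinding, allocation follows the baseline assessments, so the baseline rating precedes both allocation and exposure.

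For the interviews the protocol goes further. Under Qualitative Research: "Every effort will be made to interview both dropouts and active participants to ensure a comprehensive understanding of program acceptability". Zoom is allowed there for people who cannot attend in person. The qualitative analysis then compares those who stayed with those who dropped out on the TFA dimensions. No similar provision is stated for the questionnaires.

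On expected loss, the Sample Size Calculation states "Factoring in a 10% loss to follow-up in each group, the total sample size was estimated to be 34 participants (17 per group"), and the Intervention section reports from the team's earlier work "a retention rate of 85"%.

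**The concern.** The 8-week rating is the only score that reflects experience of HIIT. Someone who finds the sessions too burdensome, leaves and does not come to the 8-week visit contributes only an expectation recorded before the first session. If such people would have scored lower, the 8-week mean overstates how feasible, acceptable and appropriate HIIT is. The overstatement grows with the number who leave for that reason.

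What is at stake is a descriptive estimate that answers a primary objective and is meant to inform the design of a larger trial. An analysis plan can decide how to treat missing scores, but it cannot recover ratings that were never collected. The place to act is therefore the assessment schedule.

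**Working it through.** **1. The plan's own figure.** 15 per group with 10% loss: 15 / 0.90 = 16.7, rounded up to 17 per group; 2 × 17 = 34. This reproduces the stated total.

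**2. How many HIIT-arm scores may be missing.**
- Planned 10% loss (Sample Size Calculation): 17 × 0.10 = 1.7 people.
- 15% loss, from the team's earlier 85% retention (Intervention): 17 × 0.15 = 2.55 people.
- Chance that at least one of 17 is lost, if losses are independent: 1 − 0.90^17 = 0.83 at 10%; 1 − 0.85^17 = 0.94 at 15%.

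So about 2 to 3 of 17 is a fair expectation, and no loss at all is unlikely.

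**3. Bias of a responder-only mean.** Let f be the share missing, S the mean of responders, and L the mean that non-responders would have given. The mean over everyone is (1 − f)S + fL. The reported mean is S. The difference is f × (S − L).

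**4. Numbers.** The shares come from the documents or are whole persons out of 17. The gaps S − L are assumptions, because the documents give none. A gap of 4 is the arithmetic limit of a 1-5 scale.

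| Share missing | gap 0 | gap 0.5 | gap 1 | gap 2 | gap 4 (limit) |
|---|---|---|---|---|---|
| 10% | 0 | 0.05 | 0.10 | 0.20 | 0.40 |
| 15% | 0 | 0.08 | 0.15 | 0.30 | 0.60 |
| 2 of 17 (11.8%) | 0 | 0.06 | 0.12 | 0.24 | 0.47 |
| 3 of 17 (17.6%) | 0 | 0.09 | 0.18 | 0.35 | 0.71 |

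The figures are on the per-item 1-5 metric. If a scale is reported as a sum over items, the bias is multiplied by the number of items.

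**5. Interviews and scales side by side.** Both are ticked at baseline and 8 weeks in Table 1. For the interviews, the text adds dropouts and a remote route. For FIM, TFA and IAM, the text adds neither.

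**The case against.** The strongest reply is that Table 1's ticks mark nominal timepoints and do not show who can be reached. The interviews have the same ticks and still extend to dropouts. This is also a condensed article, and a withdrawal procedure may stand in a fuller document that is not shown. Both remarks are fair. They limit the point to what is written here, which extends the interviews to dropouts expressly and the scales not at all.

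Second, dropout is already visible within the primary outcomes. Retention and compliance are feasibility metrics (Table 2), and the dropout interviews are aimed at acceptability. A reader would see the score beside these. This stands and lowers the stakes. But retention shows how many left, not how they rated HIIT, and interview themes do not enter the numeric mean.

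Third, stopping HIIT is not the same as missing the visit. Nothing says that people who stop sessions are not assessed at 8 weeks, and missed sessions prompt phone calls. People may also be lost through relocation, illness or scheduling, without a low opinion of HIIT. This stands too: only those who miss the 8-week assessment lack a score, and their gap from stayers could be zero.

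Some stronger readings are tempting but unsupported:
- *The scores are inflated.* The documents give no gap between stayers and leavers, so only a risk can be claimed.
- *Leavers never rate HIIT.* They do so at baseline, in anticipation.
- *A go/no-go decision turns on the score.* No progression threshold is stated for any scale; the results are only expected to guide a later trial.
- *Control-arm or baseline ratings will be mixed into the primary mean.* The outcome sentence names neither arm nor timepoint, but that is ordinary analysis-set detail and shows no error.

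**Conclusion.** The point holds as a risk of bias that a small change to data collection would reduce. Followed as written, the plan yields no post-exposure FIM, TFA or IAM score from a HIIT participant who leaves and misses the 8-week visit, and the 8-week means contribute to a primary outcome. At the documented loss rates, and with an assumed gap of 0.5 to 2 points, the overstatement is about 0.05 to 0.30 points on the 1-5 scale, or up to 0.35 if 3 of 17 are missing. With no gap there is no bias. The calculation assumes that every lost HIIT participant lacks a score and that the overall loss rates apply to the HIIT arm. This is a worthwhile, cheap improvement to a descriptive estimate. It does not invalidate the trial's feasibility conclusions, which also draw on retention, compliance and the interviews.

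**What to change.** - Offer FIM, TFA and IAM to each HIIT-arm participant at 8 weeks or, for those who withdraw, at withdrawal or at the dropout interview already planned, in person or remotely.
- Report the HIIT-arm post-exposure mean of each scale with the number of respondents out of those randomized to HIIT.
- Show exit ratings and 8-week ratings separately as well as combined, because they follow different lengths of exposure.
- Report the baseline scores separately as anticipated ratings.

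The cost is three questionnaires for about 2 to 3 people whom the team already intends to contact. The downsides are mixed exposure lengths in the combined mean and possibly a slightly less favourable score. Dropouts who cannot be reached for interview will still be missing, which is why the number of respondents should accompany each mean.

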#### Secondary Outcomes

Between-group differences in changes in the following parameters from baseline to 8 weeks: (1) mean FPG and insulin levels, (2) indices of β cell function and insulin resistance, and (3) weight, body composition, waist and hip circumferences, and blood pressure.CGM metrics: (1) between-group differences in the proportion of time and mean time spent in nocturnal (12 to 6 AM) [50] normoglycemia (60 to <100 mg/dL) during the 8-week intervention period and the 10 days following the intervention, and (2) within-participant differences in the proportion of time and mean time spent in nocturnal (12 and 6 AM) normoglycemia (60 to <100 mg/dL) between exercise and non-exercise days during the 8-week intervention period.

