### Step 3: Screening (via In-Person Clinic Visits)

Individuals meeting the step 2 criteria will be invited to visit the GCRC at Emory University Hospital after fasting overnight for a minimum of 8 hours [29]. During the visit, participants will complete standard questionnaires to collect sociodemographic information (education, occupation, and marital status) [34,35] and details on alcohol consumption [34,35] and dietary intake [36]. Additionally, physical measurements will be conducted using standardized instruments in accordance with the World Health Organization’s STEPwise approach to noncommunicable disease risk factor surveillance (STEPS) protocol [37]. Following these assessments, individuals will undergo an oral glucose tolerance test (OGTT) and provide blood samples for insulin. Individuals diagnosed with i-IFG, defined by the American Diabetes Association criteria as FPG between 100-125 mg/dL and 2-hour plasma glucose<140 mg/dL [29], will be deemed eligible to participate in the study. Individuals without i-IFG will be excluded from further participation in the study. They will receive a summary report of their test results and general healthy lifestyle advice and will be referred to their general practitioner if they have IGT or undiagnosed diabetes for further management.

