### Continuous Glucose Monitoring

By providing 288 glucose measurements per day throughout the 8-week intervention and 10-day follow-up, continuous glucose monitoring (CGM) can track the dynamic changes in fasting glucose levels induced by HIIT [48]. This can help identify when the effects of HIIT on fasting glucose levels become evident and whether these effects are sustained after the intervention, which may not be captured by a single blood glucose measurement taken after 8 weeks. All participants, regardless of their assigned treatment, will be fitted with a CGM device on their abdominal area upon enrollment. The CGM device, Dexcom G6 Pro CGM system (DexCom, Inc), will be used in blinded mode to minimize bias and ensure that it does not influence the study outcomes. Participants will be instructed to eat their last meal by 10 PM daily after the CGM fitting. They will wear CGM devices for approximately 80 days, including 10 days prior to the intervention, the 8-week intervention period, and 10 days following the intervention. Participants will be trained on how to replace the device every 10 days, using the instructions provided in the manual [49], during the first study visit. The adequacy of CGM data will be evaluated using the following criteria: a minimum of 80% of the potential 288 glucose values per day should be present for any 7 consecutive days, commencing from the day following sensor insertion [50].

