### Statistical Analysis

#### Quantitative Research

##### Objective 1

Continuous variables will be summarized using either mean (SD) or median (IQR), depending on their distribution, which will be visually assessed through histograms. Categorical variables will be presented as counts (n) and percentages (%).

##### Objective 2

The analyses will adhere to the “intention-to-treat” principle. Between-group differences in changes in continuous variables from baseline to 8 weeks will be analyzed using mixed-effects linear regression models, while categorical variables will be assessed with log-binomial models. Skewed variables will be log-transformed prior to analysis. Fixed effects will include the study group (intervention vs control), timepoint (follow-up vs baseline), and the interaction between the study group and timepoint. Random effects will be specified for participants to account for the correlation between repeated measurements on the same individual. The *P* value for the study group-by-timepoint interaction will be used to evaluate the difference in changes between the study groups. The correlation between changes in fasting glucose levels and the indices from baseline to 8 weeks will be assessed using either Pearson or Spearman correlation coefficients, depending on the nature of the data distribution. Mixed-effects linear regression models will be used to compare CGM metrics between study groups, adjusting for baseline values. These models will also examine within-participant differences in CGM metrics between exercise and non-exercise days. Statistical significance will be considered with a 2-sided *P* value<.05 with no adjustments for the multiplicity of comparisons. All analyses will be conducted using Stata (version 18.0; StataCorp LLC).

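### The only CGM outcome is overnight time in 60 to <100 mg/dL, which serves the stated aim of tracking fasting glucose level only indirectly; mean nocturnal CGM glucose should be added

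*Protocol article*

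**What the plan says.** In the protocol article, the Secondary Outcomes section lists two CGM comparisons. One is between groups: "between-group differences in the proportion of time and mean time spent in nocturnal (12 to 6 AM) [50] normoglycemia (60 to <100 mg/dL", over the 8-week intervention and the 10 days after it. The other compares exercise with non-exercise days: "within-participant differences in the proportion of time and mean time spent in nocturnal (12 and 6 AM) normoglycemia (60 to <100 mg/dL". Table 1 (Procedures) gives the same single CGM measure: "Proportion of time and mean time spent in nocturnal (00:00-06:00) normoglycemia (60 to <100 mg/dl". No CGM outcome uses the glucose level itself.

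Entry at Step 3 of screening requires "FPG between 100-125 mg/dL and 2-hour plasma glucose<140 mg/dL", from a venous sample after an overnight fast.

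The Continuous Glucose Monitoring section gives the reason for about 80 days of wear: CGM "can track the dynamic changes in fasting glucose levels induced by HIIT". It continues: "This can help identify when the effects of HIIT on fasting glucose levels become evident and whether these effects are sustained after the intervention". It contrasts this with a single blood measurement at 8 weeks, which may miss both.

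The analysis is stated under Quantitative Research, Objective 2: "Mixed-effects linear regression models will be used to compare CGM metrics between study groups, adjusting for baseline values". The same models serve the exercise-day contrast. Laboratory fasting glucose is kept as a separate continuous outcome, "mean FPG and insulin levels", measured at baseline and 8 weeks.

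**The concern.** The sensors are there to follow the level of fasting glucose over time, but the outcome records only how long glucose lies within a band. The band stops at 100 mg/dL, where the entry range begins. Fasting glucose at screening is therefore at or above the band's upper limit in every entrant. If overnight glucose is similar, part of any reduction will take place outside the band and be counted only in part.

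Two things are at stake. First, equal reductions in glucose would count differently depending on where a participant started, so the estimate would depend on the baseline mix. Second, precision could be lost in a trial of 34 people, from data already collected. Laboratory fasting glucose cannot fill the gap for onset, persistence or exercise-day effects, because it is taken only at baseline and 8 weeks. For those three questions the band metric is the only outcome.

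The second listed form, mean time, does not help, because it carries nearly the same information as the proportion.

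**Working it through.** The protocol states no baseline time in band, detectable difference or power for the CGM outcome, so there is no figure to reproduce.

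**Inputs from the protocol.** Band 60 to <100 mg/dL; window 00:00-06:00, which is 360 minutes; 288 readings a day; entry fasting glucose 100-125 mg/dL; 15 analysed participants per group (Sample Size Calculation).

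**Inputs assumed, because the protocol does not give them.** Within-night SD *s* of 5, 10 or 15 mg/dL; nocturnal CGM mean lower than laboratory fasting glucose by 0, 5 or 10 mg/dL; treatment fall of 5 mg/dL; SD of change in nocturnal mean of 6 mg/dL.

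**Step 1: overlap of the two listed forms.** 288 readings a day is one every 5 minutes, so the window holds 72 readings. With complete data, mean time = proportion × 360 minutes. With gaps, the two differ only through missing readings.

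**Step 2: how a fall registers.** For nocturnal mean *m*, taking readings as normal within a night:

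time in band = Φ((100 − m)/s) − Φ((60 − m)/s)

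The second term is negligible here except at *s* = 15 with *m* near 100, where it takes off about 0.4 points.

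- *s* = 10, 110 to 105: Φ(−1.0) = 15.9% to Φ(−0.5) = 30.9%, a gain of 15.0 points (54 minutes a night).
- *s* = 10, 125 to 120: Φ(−2.5) = 0.6% to Φ(−2.0) = 2.3%, a gain of 1.7 points (6 minutes).
- *s* = 5, 110 to 105: 2.3% to 15.9%; 120 to 115: 0.0% to 0.1%.
- *s* = 15, 110 to 105: 25.2% to 36.8%; 125 to 120: 4.8% to 9.1%.

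The same 5 mg/dL fall is weighted by starting level, most unequally when within-night variation is small.

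**Step 3: precision.** Simulation with 15 per arm and 3,000 trials per setting. Baseline level is uniform on 100-125 plus the offset, with no average change in controls. Each metric is analysed by baseline-adjusted regression at two-sided 5%.

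| Offset (mg/dL) | Within-night SD | Power, mean glucose | Power, time in band | Loss (points) | Starting under 5% in band |
|---|---|---|---|---|---|
| 0 | 5 | 58.7% | 31.4% | 27.3 | 67% |
| 0 | 10 | 59.0% | 47.5% | 11.5 | 34% |
| 0 | 15 | 58.3% | 54.2% | 4.1 | 1% |
| −5 | 5 | 59.4% | 41.1% | 18.3 | 47% |
| −5 | 10 | 56.7% | 52.2% | 4.5 | 14% |
| −5 | 15 | 58.4% | 57.0% | 1.4 | 0% |
| −10 | 5 | 59.3% | 45.7% | 13.6 | 27% |
| −10 | 10 | 58.3% | 53.7% | 4.6 | 0% |
| −10 | 15 | 57.3% | 55.5% | 1.8 | 0% |

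Time in band has lower power in all nine settings, but in several the difference is trivial. The absolute powers are not forecasts: the assumed fall over SD of change is 5/6 = 0.83, above the 0.3 to <0.7 that the protocol takes for fasting glucose. Only the comparison between the two metrics matters.

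**The case against.** A reader might infer that participants start above the cut-off overnight and that falls ending above 100 mg/dL barely register. The documents do not support this. Entry rests on one laboratory fasting value, and the Strengths and Limitations section acknowledges day-to-day variability from a single OGTT. No CGM glucose between 00:00 and 06:00 is reported, so the starting level is unknown. Nor does a fall have to cross 100 to be seen. At a within-night SD of 8, a fall from 118 to 110 moves time in band from Φ(−2.25) = 1.2% to Φ(−1.25) = 10.6%, about 34 minutes a night. At SDs of 10-15, a 5 mg/dL fall from 105 or 110 moves it by about 12 to 19 points. Near-invisibility needs starting levels of roughly 115-125 or tight within-night variation.

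Nor does it follow that a real glucose effect would go unseen, or that the main trial would be sized on a distorted figure. Laboratory fasting glucose remains a continuous outcome, and the Sample Size Calculation ties the main trial's effect size to it.

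The band is also a defensible outcome. The Conclusions name remission as an aim of the later trial, and time in normoglycemia speaks to that more directly than a mean that may stay in the impaired range. Reporting both a proportion and minutes biases nothing.

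All of this stands, and it is a reason to keep the proportion. It does not answer the narrower point: the stated purpose of CGM concerns the course of fasting glucose level, and no listed CGM outcome measures level.

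**Conclusion.** The point holds as a mismatch between purpose and metric. The only CGM quantity is time in a band whose upper limit is the entry floor. It weights equal falls unequally, and its second form adds almost nothing. Under the assumptions shown, using it in place of mean nocturnal glucose costs between about 27 points of power and almost none. The result depends mainly on within-night variation and on how far nocturnal CGM glucose sits below laboratory fasting glucose. The protocol gives neither, so the size of the loss in this trial cannot be settled from the documents.

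This concerns secondary outcomes of a trial whose primary outcomes are feasibility and acceptability. It is a free or cheap improvement and does not invalidate the plan.

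**What to change.** In Secondary Outcomes and in Table 1, list mean nocturnal (00:00-06:00) CGM glucose in mg/dL in place of mean time in the band. Apply it to the 8-week period, the 10 days after the intervention, and the exercise versus non-exercise contrast. Keep the proportion of time in 60 to <100 mg/dL alongside it. The baseline-adjusted mixed-effects model for the group comparison and the within-participant model for the exercise-day contrast can be used as they stand.

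The cost is one new outcome line, with the same sensors, readings and models. The downside is that minutes per night is no longer listed separately; with complete data it can be recovered as the proportion × 360.
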